**Fig 5 pone.0342275.g005:**
[figure not shown]
Inclusion and exclusion criteria for patients with anorexia nervosa and healthy controls in the clinical observational trial in work package 1 of the NORMA study. AN, anorexia nervosa; BMI, body mass index; ED, eating disorder; GI, gastrointestinal; HC, healthy control; IBD, inflammatory bowel disease; NORMA, Norwegian microbiota study in anorexia nervosa. Created with BioRender.com.

Recruitment of patients with AN will be conducted at each hospital unit by hospital personnel following standardized procedures and using written material provided in the study. Most patients will be informed about the study during one of their pre-admission planning meetings, typically a few weeks before hospitalization. A few days before hospitalization or, at the latest, within the first week of treatment, patients will be contacted and asked if they wish to participate. Patients who agree to participate will provide digital informed consent granting permission to collect biological samples and retrieve information from medical records, health registries, and questionnaires. The written informed consent will also include details about the use of individual data and the storage of biological samples during the study for analysis and publication purposes.

The HC group will include healthy individuals who meet the following inclusion criteria (Fig 5): i) female, ii) age 16–50, iii) BMI equal to or above 18.5 kg/m^2^ but less than 27 kg/m^2^ (i.e., a BMI ranging from normal weight to mild overweight), iv) no previous history or treatment of EDs, and v) have sufficient proficiency in the Norwegian language to understand and complete Norwegian-language questionnaires independently. The exclusion criteria are the same as for the patients (Fig 5).

The recruitment of 90 HCs will be conducted in two phases. An initial group of HCs will be recruited primarily via a post published on the Oslo University Hospital intranet, supplemented by strategically placed posters at key locations within the hospital. Additionally, colleagues and friends may be recruited through other social networks. The second half of the HC participants will be recruited through Ås municipality and via the intranet at NMBU. The inclusion criteria concerning age will be adapted in the second phase of recruitment to ensure a more comparable age between the HC groups and patients with AN. Potential HCs will be contacted by the study researchers by email or phone and will be screened according to the inclusion and exclusion criteria. If eligible, they will sign a digital informed consent and receive all necessary information for further participation in the study.

#### Overview of study design and procedures.

The schedule of assessments in WP1 is presented in **Fig 1**. The included patients with AN will be assessed throughout their participation in standard clinical treatment at three time points (TP): before the start of treatment and/or within the first week of admission (TP1, baseline), and at 6- and 12-week follow-up (TP2 and TP3, respectively). Patients will be asked to provide fecal samples, fasting blood samples, and complete questionnaires about their mental and physical health, as well as record their diet at each time point. The HC participants will be assessed at one time point only (referred to as ‘TP1’). The HCs will complete approximately the same digital questionnaires as the patients, provide blood and fecal samples, and record their diet for three days. The NORMA study has approval to contact the participant within ten years after recruitment for follow-up data collection and access to medical records and registry data.

#### Data management.

A data management plan has been developed for the project which has been approved by the Norwegian Research Council and was part of the approval process by the Norwegian Agency for Shared Services in Education and Research (SIKT ID number 386069). The data management plan includes information about the project, responsibilities and planning, costs and resources, data collection methods and information on data storage validation and quality control. A description of how sensitive data are handled, and ethical aspects are also included. Furthermore, the data management plan includes information on data format and software, and information about the metadata, data transfer agreements, data sharing procedures and data security. Also, routines for internal and external data storage, backup and archiving are described. Finally, the regulation of intellectual property rights is described.

#### Self-report questionnaires.

Participants will receive a digital link by email to an online assessment battery consisting of eight (HC group) or ten (AN group) self-report questionnaires about different aspects of mental and physical health, GI symptoms, and stool consistency. The questionnaires are officially approved Norwegian translations. All questionnaires can be completed digitally on a computer or mobile phone. Data obtained from the online questionnaire forms will be safely collected and stored using the TSD (services for sensitive data at the University of Oslo) infrastructure and online platform. **Table 1** presents the assessment instruments, the domain captured, and the differences in the online assessment battery between the AN and HC groups.

**Table 1 pone.0342275.t001:** Self-report questionnaires to be used in the clinical observational trial in work package 1of the NORMA study.

Assessment	Assessed in	Domain
NORMA background information	AN/HC	Lifetime ED, self-reported weight, use of antibiotics and probiotics, demography
EDE-Q6.0	AN only	Current ED-symptoms
CIA.3.0	AN only	Current psychosocial impairment
GSRS-IBS	AN/HC	GI complaints and IBS-symptoms
SF-36	AN/HC	Quality of life
GAD-7	AN/HC	Current anxiety symptoms
PHQ-9	AN/HC	Current depression symptoms
OCI-R	AN/HC	Current obsessive-compulsive symptoms
NORMA Physical activity and rest	AN/HC	Physical activity and rest
Bristol stool scale	AN/HC	Stool consistency

AN, anorexia nervosa; ED, eating disorder; HC, healthy control; GI, gastrointestinal; GSRS-IBS, gastrointestinal symptom rating scale for IBS; GAD, generalized anxiety disorder; IBS, irritable bowel syndrome; NORMA, Norwegian microbiota study in anorexia nervosa; OCI-R, obsessive-compulsive inventory revised; PHQ, patient health questionnaire; SF, short form health survey.

The background questionnaire (for patients with AN and HCs) includes questions that cover various aspects such as marital status, children, education level, demography, smoking and snus habits (i.e., smokeless tobacco-product), alcohol consumption, relationship with food and body image, history of antibiotic use (both lifetime and recent), medication, and use of defecation agents.

The Eating Disorder Examination Questionnaire, version 6 (EDE-Q6.0, for patients with AN only) [53] is a 28-item self-report measure adapted from the interview-based EDE and shows strong correlation with the original version [54]. It assesses the range, frequency, and severity of ED-related attitudes and behaviors across four subscales over the past four weeks: restraint, eating concern, shape concern and weight concern. Higher global scores indicate more severe eating pathology, with a cut-off score above 2,5 suggestive of an ED [55].

The Clinical Impairment Assessment Questionnaire (CIA3.0, for patients with AN only) [56] is a 16-item self-report measure assessing psychosocial impairment related to ED features over the past 28 days. The questionnaire covers mood and self-perception, cognitive functioning, interpersonal functioning, and work performance. The total score ranges between 0 and 48, with higher scores indicating greater psychosocial impairment, and a global score of 16 or above considered to be clinically significant.

The GI Symptom Rating Scale for irritable bowel syndrome (GSRS-IBS, for patients with AN and HCs) [57] is a tool used to measure the severity of irritable bowel syndrome symptoms. The questionnaire consists of 13 self-report items that assess the severity of IBS symptoms across five subscales over the past seven days: abdominal pain, bloating, constipation, diarrhea, and satiety. Scores are rated on a 6-point Likert scale ranging from 1 to 7, with a total score ranging from 0 to 78. Higher scores indicate more severe IBS symptoms, categorized as minimal (0–20), moderate (21–39), and severe (40–78). Permission for use in the NORMA study has been obtained from AstraZeneca on 17th of July 2023.

The 36-Item Short Form Survey (SF-36, for patients with AN and HCs) [58] is a widely used self-report instrument designed to assess quality of life (QoL). The questionnaire includes 36 items that cover eight health domains over the past 4 weeks: physical activity, social activity, health problems, bodily pain, mental health, emotional problems, vitality, and general health perceptions. These are summarized into two components: physical and mental health. Higher scores reflect better QoL, though no universally accepted clinical cut-off values exist. However, scores below 40 are sometimes interpreted as indicating clinically relevant impairment.

The Generalized Anxiety Disorder Assessment (GAD-7, for patients with AN and HCs) [59] is a self-report questionnaire used to screen anxiety and assess the severity of generalized anxiety disorder. The questionnaire focuses on symptoms from the past two weeks and consists of seven questions, providing a score between 0 and 21. A score of 8 or higher is considered a reasonable cut-off for identifying probable cases of generalized anxiety disorder. The GAD-7 is a valid and reliable measure of anxiety.

The Patient Health Questionnaire 9 (PHQ-9, for patients with AN and HCs) [60] is a self-administered questionnaire that assesses symptoms of depression and is used in both clinical practice and science, and is based on the Primary Vare Evaluation of Mental Disorders (PRIME-MD) diagnostic instrument for common mental disorders. The questionnaire focuses on nine items based on the Diagnostic and Statistical Manual of Mental Disorders (DSM-IV) criteria for major depressive disorder for the last two weeks. Each symptom is scored and can give a total score between 0–27, with a score of 10 or higher as indicative of depression. The PHQ-9 is a valid and reliable measure of depression.

The Obsessive-compulsive inventory-Revised (OCI-R, for patients with AN and HCs) [61] is a self-report questionnaire consisting of 18 items which measure obsession and a variety of compulsion over the last two weeks. The symptoms are measured across six subscales; washing, checking, neutralizing, obsessing, ordering and hoarding and gives a total score between 0–72 points. A value of 21 and higher is indicative of an obsessive-compulsive disorder (OCD)-diagnosis.

The questionnaire on physical activity and rest (for patients with AN and HCs) is a self-report questionnaire consisting of eight questions about the frequency, intensity, and duration of physical activity/exercise over the past two weeks, along with 2 questions about time spent in rest/low activity. The questions on physical activity are based on a validated questionnaire from the CRC-NORDIET study [62]. The purpose of the questionnaire is to assess the level of physical activity, rest, and participants’ perceptions of rest.

The Bristol Stool Form Scale (BSFS, for patients with AN and HCs) [63] is a clinical assessment tool that classifies stools into seven groups/types, which can be used as a diagnostic tool for assessing bowel health and functioning. The different types of stool consistency provide an indication of the time spent in the colon: Types 1–2 indicate constipation, Types 3–4 are considered normal, and Types 5–7 may indicate diarrhea and urgency. The BSFS chart is a valid and reliable measure of stool consistency.

#### Dietary intake.

In addition to the self-report questionnaires, the patients with AN (at TP1–3) and HCs (at TP1 only) will be asked to digitally register their dietary intake for three consecutive days. The custom-made digital 3-day open food diary is based on a digital food diary developed by the University of Oslo. A link to the digital dietary assessment tool is sent to study participants via email, accompanied by oral instructions from health personnel and a video tutorial on how to complete the diet registration. The registration should be done continuously for three days, at all meals and use household measures for portion size estimation. Participants are encouraged to add pictures of their meals and to be as detailed as possible in their descriptions of all the food and drink consumed. However, the patients are asked not to take pictures at the hospital units to avoid disturbing/triggering other patients. Alternatively, patients with AN can opt for a food interview conducted by health personnel since patients with AN may find food self-registration challenging and potentially triggering. This interview is conducted as soon as possible after hospitalization and covers the last three days, or two days before hospitalization plus one day after. A standardized dietary interview guideline is used to ensure consistency across different hospital units.

The dietary intake data will be analyzed using the food, energy and nutrient database and calculation system NutriFoodCalc (NFC), at the University of Oslo. The NFC uses a comprehensive food composition database containing detailed information on the energy and nutrient content of foods commonly consumed in Norway. Each reported food item will be assigned to its corresponding entry in NFC using standardized food codes. The database will be used to compute total energy intake (KJ), the macronutrients protein, total fat (including saturated, monounsaturated, polyunsaturated), and carbohydrates (including sugars and fiber), and the micronutrients including but not limited to vitamins A, C, D, E, B-complex, calcium, iron, magnesium, zinc, and sodium. Foods will also be classified into predefined food groups according to NFCs classification system, enabling estimation of group-specific intake such as fruits and vegetables (fresh, frozen, canned), whole grains, dairy, meat and alternatives, and discretionary foods (e.g., snacks, sweets). Estimated portion sizes will be standardized and converted to grams per day using NFCs portion size references and coding guidelines. Intake will be calculated as a mean per participant per day, with nutrient values automatically computed based on both raw ingredients and cooked/processed forms, when applicable.

#### Fasting blood samples.

For the patients with AN, overnight fasting blood samples will be taken at their respective hospitals, and when possible, concurrently with regular blood samples as part of normal treatment procedures. In total, six blood samples will be collected at each time point (TP1–3): three serum tubes (5.0 mL with gel), two Ethylene Diamine Tetracetic Acid (EDTA) tubes (one 4.0 mL without gel and one 5.0 mL with gel), and one 4.0 mL heparin-coated vacuum tube. All the tubes will be inverted 4–5 times immediately after blood collection, stored at room temperature (19–25°C) for minimum 30 minutes (for clotting) and maximum 60 minutes, and centrifuged (15–20 minutes, 1100–1500 × g, 19–25°C) at the local hospital laboratories, except for the lithium heparin tube, which will be placed on ice immediately after sampling. The resulting supernatant from one of the serum samples will be aliquoted into five cryotubes at each hospital’s laboratory (i.e., five serum aliquots for each timepoint) and stored at −80°C, or for a maximum of 3 months at −20°C, before transportation to NMBU on dry ice. At NMBU, the serum aliquots will then be stored at −80°C for biobanking until further analysis. The remaining five blood samples will be analyzed at the local laboratories.

For the HCs, overnight fasting blood samples will be taken at the Regional Department of Eating Disorders at Oslo University Hospital by nurses or students who have completed an approved course in blood sampling. The HCs will collect the same blood sample types as the patients with AN, except no heparin tube, and follow the same procedures as described for the patients including aliquoting serum samples for biobanking at NMBU until further analysis. The remaining blood samples will be analyzed at the Department of Medical Biochemistry at Oslo University Hospital.

Blood serum is chosen for biobanking due to its accessibility and suitability for analyzing a wide range of biomarkers, including inflammation- and appetite-related markers. To ensure proper handling and storage of blood samples, all specimens collected at local hospitals will be processed at accredited laboratories and stored according to standard operating procedures (SOPs). Key biomarkers that will be analyzed in serum samples at the local laboratories (for patients with AN) or at the Department of Medical Biochemistry at Oslo University Hospital (for HCs) are presented in **Table 2**. Additional analyses will include, but not be limited to, biomarkers related to appetite and satiety (e.g., ghrelin, adiponectin, GLP-1, and leptin), inflammation (e.g., calprotectin, IL-1β, MCP-1, and RANTES), and gut permeability (e.g., LBP and I-FABP).

**Table 2 pone.0342275.t002:** Key biomarkers to be analyzed in blood serum samples from patients with anorexia nervosa and healthy controls the clinical observational trial in work package 1 of the NORMA study.

Biomarker group	Biomarkers	Rationale
Hematology	Hemoglobin (Hb), mean corpuscular volume (MCV), mean corpuscular hemoglobin (MCH), hematocrit (HCT), erythrocyte volume fraction (EVF), thrombocytes, B-differential count, ferritin, international normalized ratio (INR)	Nutrient status (anemia), dehydration, infections/inflammatory state
Hormones	thyroid-stimulating hormone (TSH), triiodothyronine (T3), thyroxine (T4), parathyroid hormone (PTH)	Metabolism, hypo-and hyperthyroidism
Electrolytes	Sodium, calcium, potassium, magnesium, phosphate, chloride, Osmolality/osmol gap	Nutrients status, dehydration, electrolyte imbalance, Risk of refeeding syndrome
Lipids	Total cholesterol, low-density lipoprotein (LDL), high-density lipoprotein (HDL), triglycerides	Cholesterol status, cardiovascular risk
Metabolites	Creatinine, bilirubin, carbamide	Kidney function, muscle metabolism, liver disease
Enzymes	Alanine transaminase (ALT), aspartate transaminase (AST), gamma-glutamyl transferase (GGT)*, lactate dehydrogenase (LDH), creatine kinase (CK), amylase, alkaline phosphatase (ALP)*, glomerular filtration rate (GFR)*	Liver and kidney function, muscle injury
Proteins	Albumin, C-reactive protein (CRP)	Nutrient status and inflammatory state
Vitamins	Vitamin D*, cobalamin (B12), folate	Vitamin status, bone health, anemia
pH*	Arterial blood gas (ABG), partial pressure of carbon dioxide (PaCO_2_) and bicarbonate (PaHCO_3_) in arterial blood, base excess (BE)	Lung-function, acid-base balance (acidosis/alkalosis)
Carbohydrates	Glucose	Nutrient status, fasting blood sugar

NORMA, Norwegian microbiota study ta in anorexia nervosa.

*Only analyzed for patients with anorexia nervosa, not healthy controls.

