**Methods:**

NORMA is a collaboration between the Norwegian University of Life Sciences and seven Norwegian specialized eating disorder inpatient treatment units, consisting of three work packages (WP): a clinical observational trial (WP1), in vitro fermentation experiments (WP2), and animal experiments (WP3). In WP1, 90 patients with AN (age 16–50, BMI < 18.5) admitted for treatment and 90 healthy controls (HCs, age 16–50, BMI 18.5–27) will be recruited. Data on mental and physical health, dietary intake, and blood and fecal samples for biomarker and microbiota analyses will be collected at baseline, 6 and 12 weeks after start of treatment for AN patients and once for HCs. Outcomes will be compared between groups, and longitudinal effects of standard treatment examined within the AN group. In WP2, fecal microorganisms from patients and HCs will be grown *in vitro* to assess influence of prebiotics. In WP3, mice will receive fecal microbiota from AN and HC donors to determine if and how AN‑related microbiota affects AN‑relevant phenotypes.

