## Methods

### The NORMA study

The NORMA study consists of WP1; a clinical observational trial (**Fig 1**), WP2; in vitro experiments (**Fig 2**), and WP3; animal experiments (**Fig 3**). An overview of all WPs is presented in **Fig 4**. The NORMA study is led by the Norwegian University of Life Sciences (NMBU) and conducted in collaboration with seven specialized inpatient EDs treatment units across six hospitals in Norway, located in Oslo, Bergen, Vikersund, Levanger, Bodø, and Gjøvik. Additional collaborators are The University of Oslo, Karolinska Institute and the Norwegian user organizations for eating disorders ROS and SPISFO, which has been involved in the planning of the study. WP1 includes a cross-sectional design that will investigate the microbial composition of the gut in patients with AN in comparison with HCs, and a clinical observational trial that will investigate how the composition is affected by standard care treatment in AN longitudinally (one group time-series design). We will then apply preclinical models in WP2 (in vitro fermentation experiments) and WP3 (animal experiments) based on fecal material from WP1. The first results are expected to be generated during second quarter of 2026.

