#### Study participants.

In WP1, a total of 90 patients with AN referred to specialized treatment for ED and 90 HCs will be recruited. Participant recruitment and data collection began on September 1st, 2023, and are expected to be completed by May 31st, 2026.

Patients with a primary diagnosis of AN referred to one of the six collaborating hospitals and who presumably will be under inpatient treatment for at least 12 weeks are eligible for inclusion. The collaborating hospital units include The Regional Department of Eating Disorders (Oslo University Hospital, Oslo), The Regional Department of Eating Disorders (Haukeland University Hospital, Bergen), Regional Center for Eating Disorder (Nordland Hospital Trust, Bodø), The Regional Eating Disorders Unit (Nord-Trøndelag Hospital Trust, Levanger), Modum Bad (Vikersund), District Psychiatric Center (Innlandet Hospital Trust, Gjøvik), and District Psychiatric Center (Oslo University Hospital, Søndre Oslo, Oslo). Both inpatients and patients receiving intensive day treatment are eligible for inclusion. This also includes ‘sequential inpatients’, referring to patients who are hospitalized for 4–6 weeks, then return home for a period, and are subsequently re-hospitalized. The inclusion criteria for the patients are i) female ii) diagnosed with AN (both restrictive and binge-eating/purging type), iii) age 16–50, iv) a body mass index (BMI) below 18.5 kg/m^2^, and v) sufficient proficiency in the Norwegian language to understand and complete questionnaires in Norwegian independently. The exclusion criteria are i) history of inflammatory bowel disease, celiac disease, or GI tract surgery, ii) treatment with oral antibiotics in the past two months, or iv) systematic intake of probiotic supplements in tablet form in the past two months. The inclusion and exclusion criteria are summarized in **Fig 5**.

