#### Hypotheses and planned statistical data analyses in WP1.

The clinical observational trial in WP1 is designed to test the following hypotheses.

WP1, Hypothesis 1: The gut microbiota in patients with AN is different from that of HCs. We will compare different indices of alpha diversity, investigating both microbial richness and evenness, and different measures of beta diversity. Also, differences in bacterial abundances at various taxonomic levels (e.g., phylum, class, order, family, and genus) will be investigated using conventional statistical approaches as well as more advanced multivariate methods.WP1, Hypothesis 2: Inpatient treatment of patients with AN combining cognitive treatment with re-nutrition strategies will change the gut microbiota in a more normalized direction (more similar to HCs). Mixed models will be applied to statistically analyze the effect of time on different indices of alpha diversity and bacterial abundances at various taxonomic levels (e.g., phylum, class, order, family, and genus) with and without adjusting for baseline characteristics such as age and BMI. Differences in the overall bacterial communities between the patients with AN at the different visits and HCs based on the beta diversity measures will be assessed using methods such as global permutation based multivariate analysis of variance (PERMANOVA).WP1, Hypothesis 3: Gut microbiota composition in patients with AN at TP1 (before treatment) is associated with serum biomarkers such as biomarkers of appetite regulation and inflammation, dietary characteristics, GI issues, and mental issues, and can be used to predict treatment success in terms of improved BMI and EDE-Q-scores. Associations between relevant parameters will be analyzed using multivariate analysis such as principal components analysis (PCA), canonical variate analysis, independent components analysis, and multivariate regression. Regression models will be used to investigate associations between microbial diversity and clinical outcomes, adjusting for age and BMI. Machine learning approaches such as partial least squares regression, gradient boosting, or artificial neural network algorithms will be used to predict the response variables (clinical outcomes and treatment success), from the large set of predictor variables; microbial taxa, gene, or pathway content.WP1, Hypothesis 4: Changes in microbiota composition during inpatient treatment towards that of HCs are associated with improvements in BMI as well as improvements in dysregulated serum biomarkers, GI complaints, and mental health. Associations will be analyzed using similar strategies as described in hypothesis 3.

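### AN-HC differences in the Table 2 blood markers are partly confounded with laboratory, because patients are assayed locally and all controls in one Oslo laboratory

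*Protocol article*

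**What the plan says.** Under 'Fasting blood samples', one serum tube per patient visit is set aside for the biobank, and its supernatant "will be aliquoted into five cryotubes". Of the other patient tubes the article says "The remaining five blood samples will be analyzed at the local laboratories". For controls, who follow the same procedures apart from the heparin tube, it says "The remaining blood samples will be analyzed at the Department of Medical Biochemistry at Oslo University Hospital". The text introducing Table 2 repeats the split: the key markers are analysed "at the local laboratories (for patients with AN) or at the Department of Medical Biochemistry at Oslo University Hospital (for HCs").

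Patients come from "seven specialized inpatient EDs treatment units across six hospitals in Norway". Two of these units belong to the hospital that assays the controls: "The Regional Department of Eating Disorders (Oslo University Hospital, Oslo") and the district psychiatric centre at Søndre Oslo.

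The abstract says "Outcomes will be compared between groups, and longitudinal effects of standard treatment examined within the AN group". Hypothesis 4 links microbiota change to "improvements in dysregulated serum biomarkers, GI complaints, and mental health". Table 2 covers patients and controls, and an asterisk marks the items measured in patients only. Accredited laboratories and standard operating procedures are mentioned as safeguards for handling and storage.

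**The concern.** Every control value for a Table 2 marker comes from one laboratory. A patient at any of the five units outside Oslo University Hospital is measured somewhere else. For those patients diagnosis and laboratory coincide, so no model fitted to their values and the control values can separate the two. Accreditation and standard procedures govern how a sample is handled; they do not put different analysers on one calibration.

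Any average offset between the outside laboratories and the Oslo laboratory enters the AN-HC difference directly and would be read as an effect of AN. A larger sample does not remove the offset and makes a false positive more likely. If an AN-HC contrast were also used to choose which markers count as dysregulated, the offset could influence what is carried into Hypothesis 4.

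**Working it through.** The article gives no figure on this point to reproduce. The check has two parts: which analyses the laboratory split touches, and how large the effect could be under stated assumptions.

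**What is touched**

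- *Unstarred Table 2 markers, AN versus HC:* touched. The laboratory differs by group for patients at 5 of 7 units, and possibly for all patients, because the article does not say that the Oslo units use the controls' laboratory.
- *Starred Table 2 markers* (GGT, ALP, GFR, vitamin D, the blood-gas group): not touched, because there are no control values.
- *Primary outcomes:* not touched. The only AN-HC primary outcome is fecal microbiota; the others are changes within patients.
- *Change from TP1 to TP3 within a patient:* not touched as long as the patient's samples stay with one laboratory.
- *Appetite, inflammation and permeability markers such as ghrelin, leptin, IL-1β and LBP:* listed as additional analyses outside Table 2. Serum from both groups is banked at NMBU, so the Table 2 split does not apply to them. CRP is the inflammation marker that does sit in Table 2.
- *Hypothesis 4:* touched only if dysregulated is defined by the AN-HC contrast of a Table 2 marker.

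**Illustrative size**

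From the article: 90 per group, about 10% drop-out (90 × 0.9 = 81), α = 0.05, seven units of which two belong to Oslo University Hospital. Assumed: a two-sided test, equal recruitment across units (so 5/7 of patients are assayed elsewhere), Oslo patients sharing the controls' laboratory, a between-person CV of 25%, and mean offsets of 3%, 5% and 10% outside Oslo.

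Spurious difference in SD units: d = (offset / CV) × 5/7.

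- 3%: 0.12 × 5/7 = 0.086
- 5%: 0.20 × 5/7 = 0.143
- 10%: 0.40 × 5/7 = 0.286

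With SE = √(2/81) = 0.157, the chance of nominal significance when there is no true difference is 1 − Φ(1.96 − d/SE) + Φ(−1.96 − d/SE), which gives 8.5%, 14.9% and 44.4%.

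Only the ratio of offset to SD matters, so the table below varies that ratio and the share of patients assayed outside the controls' laboratory (90 per group, rejection rate per marker):

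| Offset (SD) | Half of patients | 5/7 | All |
|---|---|---|---|
| 0.1 | 6.3% | 7.7% | 10.3% |
| 0.2 | 10.3% | 16.0% | 26.9% |
| 0.3 | 17.2% | 30.1% | 52.1% |
| 0.5 | 38.9% | 66.9% | 91.8% |

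**Precision of an Oslo-only contrast**

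With equal recruitment, 2/7 × 90 ≈ 26 patients. The detectable difference at 80% power is (1.96 + 0.84) × SE. For 90 versus 90, SE = √(2/90) and the result is 0.42 SD. For 26 versus 90, SE = √(1/26 + 1/90) and the result is 0.62 SD.

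**The case against.** The strongest reply is that no AN-HC contrast of a Table 2 marker is a listed primary or secondary outcome. Serum biomarkers enter the outcomes only through their associations with microbiota, and the case for a group comparison rests on one general sentence in the abstract and on the layout of Table 2. This limits the reach of the point but does not remove it. Markers are measured in controls and those not measured are singled out, so some comparison is likely.

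Second, the panel is largely routine. Patient blood is drawn with clinical samples where possible, results come from medical records, and controls receive a health report. Local assay is a reasonable choice for those purposes and need not be abandoned.

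Third, an analysis plan may add laboratory or site adjustment, since the covariates named in the hypotheses section are only examples. That helps where some patients share the controls' laboratory. It cannot separate group from laboratory for the others.

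Two stronger readings are tempting. A reader might infer that group and laboratory are fully confounded; the two Oslo University Hospital units make this unsupported, although the article does not confirm the overlap either. A reader might also infer that dysregulated in Hypothesis 4 must mean different from controls. The term is undefined and could equally rest on reference ranges, and the biomarker types named in Hypothesis 3, appetite regulation and inflammation, lie mostly outside Table 2.

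Finally, the offsets and the CV are assumptions, and one CV cannot stand for markers as unlike as sodium and creatine kinase. That is correct.

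**Conclusion.** For Table 2 markers measured in both groups, an AN-HC difference is partly confounded with laboratory, and the article states nothing that would separate the two. This follows from the text alone. The 9%, 15% and 44% rejection rates are illustrations under a 25% CV, offsets of 3%, 5% and 10% and equal recruitment; they are not estimates for the panel. The true effect could be negligible for well-standardised markers, or larger if the Oslo units do not share the controls' laboratory. The point concerns the interpretation of secondary blood-marker comparisons. It does not weaken the microbiota comparison or the longitudinal analyses. Hypothesis 4 is exposed only if its undefined term is given an AN-HC meaning for a Table 2 marker.

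**What to change.** Keep the routine local panel and make these changes:

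1. Record the assay laboratory for every Table 2 result, and state whether patients at the Oslo University Hospital units are assayed in the controls' laboratory.
2. For any Table 2 marker compared with controls, report beside the all-unit contrast a sensitivity contrast limited to patients assayed in the controls' laboratory. Do not attribute to AN a difference seen only in the all-unit contrast.
3. For the few serum-measurable markers that will be put forward as AN-HC differences or used to define dysregulated, assay banked TP1 patient serum and control serum in one laboratory, with groups mixed within runs, where aliquot volume allows.
4. Define dysregulated in Hypothesis 4 without relying on cross-laboratory differences.

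Recording and reporting cost almost nothing. The central run costs reagents and aliquots that the additional biomarker panel also needs; the article gives no volumes, so feasibility has to be checked. Blood counts and INR cannot be run on banked serum and depend on the sensitivity contrast alone. That contrast is imprecise (about 26 patients under equal recruitment; detectable difference 0.62 against 0.42 SD), so it should not replace the all-unit contrast as the main analysis, and a non-significant result in it is not evidence of no difference.
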